### Quantitative assessments and analytic plan

Quantitative data on feasibility (including recruitment, retention, adherence, and contamination) and safety of the intervention will be gathered through study records pertaining to recruitment, adherence, retention and safety. Data on empowerment of DILs and Mils (knowledge about safety and the links between DV and health, gender-equitable attitudes, decision-making skills, communication and social support, and resistance to DV) and incidence of DV and related health outcomes (e.g., quality of life, anxiety and depression, and maternal and infant health) will be gathered by research interviewers not involved in intervention implementation through face-to-face interviews. Interviews with DILs and MILs will be conducted individually at enrollment and 3 months and 6 months postpartum. Measures were chosen based on our theoretical approach and drawn from instruments used in our previous research, the Indian National Family Health Survey and studies of GBV and health in India and elsewhere (Table 3). Questions were selected keeping in mind the need to minimize study participation-related risks. For example, questions regarding MILs’ perpetration of violence will only be posed to DILs, and MILs’ experience of DV will also be posed in order to monitor safety of the intervention.

**Table 3 T3:** Measures

**Measure**	**DIL**	**MIL**
**Feasibility and Safety**		
Recruitment, adherence, retention (proportion of eligible individuals who enroll, sociodemographic comparison of enrollees and non-enrollees, adherence to intervention and data collection visits, attrition)	X	X
Safety (e.g., number and nature of safety-related events)	X	X
Contamination (knowledge of neighbors, friends, or relatives participating in the intervention arm)	X^a^	X^a^
**Individual-level Indicators of Empowerment**		
Demographic indicators of access to resources (e.g., age, marital duration, parity, education, employment, socioeconomic status, household structure and husband’s age, education and income [27])	X	X
Knowledge and perceptions of DV & family Health (e.g., knowledge and perceptions of reproductive and infant health [27], links between DV and health)	X	X
Gender-equitable attitudes (modified version of the Gender Equitable Male [GEM] scale [50])	X	X
Decision-making (involvement in household decisions [27], DILs’ involvement in food-related decision-making, household food insecurity access scale [51])	X	X
Freedom of movement (indicators of mobility [52])	X	X
**Interpersonal- and Family-level Indicators of Empowerment**		
Social support (DILs’ perceptions of social support and MILs’ provision of emotional and practical support using an adapted Multidimensional Scale of Perceived Social Support [53])	X	X
Communication (indicators of communication between MILs and DILs and with sons/husbands regarding household matters)	X	X
Resistance to violence (DILs’ overt and covert resistance to DV and MILs’ opposition to DV by their son)	X	X
**Outcomes**		
Domestic violence (measures of physical, sexual, and psychological acts of violence perpetrated by husbands, MILs, or other family members using an adapted Conflict Tactics Scale [54])	X	X
Perceived quality of life (WHOQOL-BREF [55])	X	X
Anxiety and depression (Kessler Psychological Distress Scale – K10)	X	X
Postnatal Depression (Edinburgh Postnatal Depression Scale [56])	X	
Maternal and Infant Health (maternal height, weight, weight gain during pregnancy, and BMI; infant weight, length, and head circumference)	X	

^a^Assessed only among control arm MILs and DILs.

Descriptive analyses will be conducted on data related to Aim 1 while data for Aims 2 and 3 will be analyzed using the intention to treat approach. Appropriate statistical techniques will be used to compare study arms on outcomes of interest (DILs’ and MILs’ empowerment, DV incidence, quality of life, anxiety and depression and maternal and infant health status) and, tailored by whether the outcome is binary, categorical, or continuous. Analytic models of intervention effect will include adjustments for individual-level demographic and background variables, such as age, education, and socioeconomic status, measured at baseline prior to randomization to examine for improved precision and to adjust for any (random) covariate imbalance across groups [57]. Longitudinal measurements of outcomes will be exploited using statistical techniques for matched or longitudinal analysis (matched pair analysis, before-after comparisons, generalized estimating equations for longitudinal models) to assess whether additional precision in efficacy estimates is possible. Finally, in the intervention group, we will explore the association between number of sessions attended by MILs and DILs and DV incidence to examine possible dose–response.

Prior to estimating program effects, simple statistics (e.g., means, variances, frequencies, correlations) will be examined to characterize DILs and MILs on various measures (including the experience of different types of DV by perpetrator) and to summarize indicators of feasibility and safety. The distributional properties and reliability of continuously scaled variables will be examined. We will verify that intervention and control groups do not differ on important baseline characteristics that would complicate the evaluation. Bivariable relationships will be examined using chi-square tests for categorical variables and two sample t-tests or Wilcoxon Rank Sum tests, as appropriate, for continuous variables. Highly collinear (r>0.5) variables will be identified so as not to be included together in subsequent analyses.

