***Dil Mil *****Causal Model.**

## Methods/design

### Study setting and design

Our research is being conducted in Bengaluru, the third most populous city in India with a population of over 8.5 million [40]. Among urban women aged 18 to 29 in the state of Karnataka, about 30% were married by age 18 and 17% had received no schooling [2]. Antenatal care utilization is high; 71% of urban women had their first antenatal care visit in the 1st trimester [2]. The municipal government of Bengaluru operates a network of 36 urban primary health centers, all of which offer antenatal and postpartum services [41]. These centers are located in the middle of clusters of lower income, working class neighborhoods with populations ranging between 60,000 to 90,000. Women residing in these neighborhoods engage in home-based work or are employed as domestic workers or in the construction or garment industry, and men are involved in a range of unskilled and semi-skilled occupations such as manual labor, masonry, and carpentry.

A phase 2 randomized controlled trial using a parallel comparison of the *Dil Mil* intervention versus standard care will be implemented in three public primary health centers in Bengaluru. Figure 2 describes the flow of study activities. Table 1 summaries the ways in which the design responds to ethical challenges involved in research on interventions to mitigate DV. DIL-MIL dyads will be randomized either to the control arm and receive standard care or to the intervention arm and receive standard care plus the *Dil Mil* intervention. Our prior research in these centers showed that risks are minimized when research is conducted in this setting since accessing care at the centers is well accepted in the community and there is little scrutiny of activities conducted within their four walls.

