### Randomization

Consenting dyads will be randomized as pairs on completion of the baseline assessment. Within each site, dyads will be randomized to ensure treatment balance after every 20 randomizations. The study statistician will employ a pseudo-randomizer software package to determine dyad treatment assignments and provide a series of sealed opaque randomization envelopes to study staff with one envelope per dyad. The participant IDs will be printed on the outside of the envelope, and the assigned study arm will be printed on a card contained in the envelope. A designated staff member at each center will open envelopes in sequential order of participant ID. Post randomization, the project director will ensure that the staff designated to facilitate intervention sessions do not conduct follow-up interviews or vice versa, and interviewers will not have access to information on treatment assignment.

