### Sample size and power analysis

We conducted a power analysis based on the proposed sample size of 144 dyads. Our analysis of feasibility and safety (Aim 1) will use descriptive statistics and comparisons between arms without predetermined expectations regarding statistical power. In contrast, data related to Aims 2 and 3 will be analyzed using the intention to treat ( ITT) principle [48,49]. Power calculations, performed assuming a significance level of 0.05, 90% retention, and no contamination, indicated that we have sufficient statistical power to detect changes in intermediary outcomes , that is, indicators of DILs’ and MILs’ empowerment (e.g., proportion of DILs who report that wife beating is unjustified). If 45% of DILs in the control arm report that wife beating is unjustified [27], we will be able to detect a relative risk of 1.6 with 88% power. Due to resource and time constraints of a phase 2 trial, we did not power the trial to detect a significant effect on DV. Nevertheless, we estimated power calculations for DV among DILs during the first 6 months postpartum based on the literature. Given the proposed sample size, we will be able to detect a relative risk of 0.5 with power ranging from 23% to 95% when the proportion reporting DV in the control arm ranges from 20% to 50%.

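### The effect models are not committed to adjusting for the baseline outcome or the health centre, and before-after and matched-pair comparisons are left open as ways to gain precision

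*Protocol article*

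**What the plan says.** Under Quantitative assessments and analytic plan, in the text after Table 3, the protocol article states: "Analytic models of intervention effect will include adjustments for individual-level demographic and background variables, such as age, education, and socioeconomic status". The stated purpose is "to examine for improved precision and to adjust for any (random) covariate imbalance across groups". The next sentence turns to the repeated measurements and lists "matched pair analysis, before-after comparisons, generalized estimating equations for longitudinal models", to be used "to assess whether additional precision in efficacy estimates is possible". It neither ranks these methods nor says how baseline would enter the GEE.

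Two other places matter:

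- **Design.** The trial "will be implemented in three public primary health centers in Bengaluru", and the Randomization section says "Within each site, dyads will be randomized to ensure treatment balance after every 20 randomizations". Health centre is therefore a stratification factor.
- **Data collection.** "Interviews with DILs and MILs will be conducted individually at enrollment and 3 months and 6 months postpartum". Randomisation follows the baseline assessment, so enrolment values of the attitude, support, decision-making, quality-of-life and distress scales are proper pre-randomisation covariates.

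**The concern.** The covariates are described as a class of personal background characteristics. Health centre is not a personal characteristic. A baseline attitude or distress score does not fit naturally either, since Table 3 lists the demographic indicators separately from the scales. Yet the baseline value of the same outcome is usually the strongest predictor available, and health centre is the one factor that the randomisation itself uses.

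The article looks for precision from the repeated measurements in a set of methods that includes before-after and matched-pair comparisons. Those can be less precise than adjusting for baseline, and can even lose precision against ignoring baseline.

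The trial is small, and the Discussion makes the case for phase 3 depend partly on effects on the empowerment outcomes and on the direction of trends in violence and health. Precision that costs nothing is worth securing here.

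**Working it through.** **Inputs from the article.** "We conducted a power analysis based on the proposed sample size of 144 dyads". Retention is 90% and the significance level 0.05 (Sample size and power analysis). I assume equal allocation and a two-sided test. Analysed per arm: 144 × 0.9 / 2 = 64.8.

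**The article's own power figure.** Control 45%; relative risk 1.6 gives 0.45 × 1.6 = 72%. With pooled proportion 0.585:

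z = [0.27 × √64.8 − 1.96 × √(2 × 0.585 × 0.415)] / √(0.45 × 0.55 + 0.72 × 0.28) = (2.173 − 1.366) / 0.670 = 1.205

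This gives 88.6% power, in agreement with the stated 88%. The point does not dispute that figure; the calculation only confirms the working sample size.

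**Variance of three between-arm estimators.** Take a continuous outcome with equal variance at baseline and follow-up, and correlation r. Relative to comparing follow-up values alone:

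- follow-up only: 1
- difference in changes: 2(1 − r)
- baseline-adjusted: 1 − r²
- changes against adjusted: 2(1 − r)/(1 − r²) = 2/(1 + r)

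The power columns fix the effect at the size that a follow-up-only comparison detects with 80% power: (1.960 + 0.842) × √(2/64.8) = 0.49 SD.

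| r (assumed) | Change, variance | Adjusted, variance | Ratio | Change, power | Adjusted, power |
|---|---|---|---|---|---|
| 0.2 | 1.60 | 0.96 | 1.67 | 60% | 82% |
| 0.3 | 1.40 | 0.91 | 1.54 | 66% | 84% |
| 0.5 | 1.00 | 0.75 | 1.33 | 80% | 90% |
| 0.7 | 0.60 | 0.51 | 1.18 | 95% | 97.5% |
| 0.8 | 0.40 | 0.36 | 1.11 | 99.3% | 99.7% |

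The change factor 2(1 − r) exceeds 1 whenever r is below 0.5, so in that range taking changes is worse than ignoring baseline. The ratio 2/(1 + r) is above 1 for every r below 1, so in large samples baseline adjustment is never the less efficient choice.

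**Health centre.** A simulation used three centres of 48 dyads, blocks of 20 within centre, 10% random loss, a continuous outcome with no treatment effect, and 20,000 runs. When centre explained 0, 1, 5 and 10% of the outcome variance (assumed shares), the test that ignores centre rejected in 5.1, 5.1, 4.8 and 4.1% of runs. With centre in the model, the rate was 5.0 to 5.2% throughout.

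**The case against.** The strongest reply is that this is condensed wording. The covariates are given as examples, so baseline outcome and health centre are unspecified rather than ruled out, and an analysis plan that is not shown may name them. This stands in part: a reader might infer that the plan excludes both, and the text does not say so. What remains is that the article states a class that does not naturally contain either, and actively names before-after and matched-pair comparisons as routes to precision. That is a stated choice, not just missing detail.

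Other stronger readings also fail:

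- **Before-after comparison replaces baseline adjustment.** It does not. The longitudinal methods are an additional step, and GEE is one of them. GEE can condition on baseline.
- **Within-arm changes will be read as treatment effects**, mixing the intervention with the shift from pregnancy to postpartum. The article speaks of comparing study arms, and a between-arm comparison of changes removes a shift common to both.
- **The favourable estimator will be selected.** Looking at whether precision improves is not a rule to report whichever result suits.
- **About 21 participants per arm are given up**, from 64.8/0.75 = 86.4. That needs r = 0.5 and an unadjusted follow-up comparison as the alternative, whereas the plan already includes covariate adjustment and GEE.
- **Omitting health centre invalidates the test.** The error rate stayed between 4.1 and 5.1%.

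It is also true that the variance formulas are for continuous outcomes, while the article's power examples are proportions, and that some outcomes have no baseline value.

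**Conclusion.** The point holds as a recommendation to improve the specification, not as an error or contradiction. The article does not commit to adjusting for baseline outcome or health centre, and it leaves weaker longitudinal comparisons open beside GEE without choosing.

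For continuous outcomes measured at enrolment, taking the before-after route would cost 11% more variance than baseline adjustment at r = 0.8, 33% at r = 0.5 and 54% at r = 0.3. These sizes rest on assumed correlations, equal variances at the two times and large-sample formulas. They compare two methods and are not an estimate of what the plan as a whole will lose. No size is claimed for binary outcomes. Including health centre mainly removes a small conservatism.

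**What to change.** Specify one between-arm model per outcome, for example GEE or a mixed model on the 3- and 6-month values, with:

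- arm, visit and arm-by-visit;
- health centre (three levels);
- the demographic covariates already named;
- the baseline value of the same outcome, where one is measured.

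Two cases need their own line. For domestic violence, use a baseline score or a recent-period measure: ever having experienced violence is an eligibility criterion (Table 2), so an ever/never indicator would not vary. For outcomes with no baseline value (postnatal depression, infant measures), adjust for health centre and the demographic covariates; baseline Kessler distress score is optional for postnatal depression.

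State that before-after and matched-pair comparisons will not be used as effect estimators.

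The cost is wording in the analysis plan. The interviews and the randomisation record already supply the variables, so no new data are needed.

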### Qualitative assessments and analytic plan

We will gather in-depth information on study implementation-related issues that complement the quantitative data through three sets of 10 in-depth interviews (n=30) after the 6-month postpartum evaluation [58]. They include the following: (1) To better understand participants’ experience with and feedback on the intervention and its effectiveness, we will select, from the intervention arm, 5 DILs and 5 MILs who participated in all intervention sessions for an in-depth interview. These data will contribute to the refinement of the intervention curriculum to maximize its potential impact on DV. (2) To assess logistical, DV-related, or other barriers to intervention adherence and retention for improving a future phase 3 trial, we will interview 10 intervention arm participants who did not attend all scheduled sessions (that is, MILs who attended fewer than 5 sessions and DILs who attended only 1 or 2 out of 3 sessions, assuming they are not lost to follow-up). (3) To examine the presence of contamination, we will interview 10 DILs and MILs in representative proportions drawn from those control arm participants who reported knowing neighbors, friends, or relatives participating in the intervention arm at the 6-month postpartum interview. These interviews will focus on assessing extent of knowledge regarding the content of the intervention and ways in which this information may have influenced participants’ perspectives on gender equity and family relationships and perpetration and experience of DV.

In-depth interviews will be audio-taped, transcribed verbatim, translated into English, and imported into ATLAS.ti®. Analysis will be carried out using the following steps: (1) data immersion through repeated readings of transcripts and associated field notes until content familiarity is high; (2) summarization of key themes that emerge in the narratives in the form of theoretical and analytical memos for each major category; (3) development of codes and a codebook with definitions through team discussion of key themes and based on memos, using a combination of inductive and deductive approaches; the coding structure will be hierarchically ordered so that additional dimensions of meaning can be examined separately and so that new codes can be added as data collection and analysis progress; (4) coding by two senior staff, using steps described by Carey et al. [59], to ensure intercoder agreement; (5) generation of meaning from coded data by examining variation within each theme/code and differences between individuals/subgroups; comparison and categorization will be facilitated by the summarization of data through diagrams and tables; and (6) interpretations and key lessons regarding intervention quality, feasibility and adherence, and contamination extracted through the above process and discussion within the investigative team [60-62].

## Discussion

This study will evaluate the feasibility, safety, and potential effectiveness of an innovative women’s empowerment intervention to mitigate DV and related adverse health outcomes. The intervention has been developed on the basis of our past research in India and successful experiences in DV prevention in other parts of the world. The planned phase 2 trial will enable us to evaluate the feasibility, safety, and potential effectiveness of the intervention and is a necessary prerequisite for a phase 3 trial, providing evidence critical to its design, including preliminary data on effect sizes and the potential for contamination.

In our phase 1 pilot study, we established the acceptability of the *Dil Mil* intervention and demonstrated that it is likely safe. However, due to the limited sample size and participant follow-up, safety concerns remain. Empowering young women can result in backlash from their husband and his family. Although the risk for backlash is minimized by the inclusion and empowerment of MILs, a careful study of safety is warranted. The *Dil Mil* trial has been designed keeping in mind research-related risks and incorporating an array of strategies to reduce these risks as well as to monitor and measure safety. Thus, this study offers approaches that may help guide safety planning and monitoring in other domestic violence intervention trials in similar settings. Moreover, given the staggeringly high prevalence of DV among young women in India (and indeed globally) and the dearth of data on effective interventions, this study is poised to make an important contribution to the evidence-base for DV prevention.

Enrolling pregnant women is a compelling approach because of the growing utilization of primary health care and especially antenatal services in India, the fact that women in India tend to marry young and bear children early in their relationship, and the acceptability of DV prevention as part of maternal and child health promotion. Although testing our intervention in this population will limit the generalizability of our results, we believe that the strengths of this approach outweigh the attendant limitation.

As is typical of phase 2 trials, we will have limited statistical power to evaluate the effect of the intervention on DV, but substantially greater statistical power to examine the effect on intermediary outcomes (DILs’ and MILs’ empowerment). These results will provide important insights into whether and how the intervention might have an effect.

Our study does have several limitations. Evaluations of empowerment-based DV interventions on which *Dil Mil* is based indicate that the effect of the intervention at least on intermediary outcomes will be manifest by 6 months postpartum [38,40]. We recognize that a longer follow-up might be preferable for a future, more resource-intensive phase 3 trial. Further, DIL-MIL dyads enrolled and retained in this study may represent those who are at relatively lower risk of DV. We will elicit qualitative feedback from participants on recruitment strategies to improve our ability to reach the most vulnerable young women in the future. In our prior longitudinal study, women with a history of DV were no more likely to be lost to follow-up than other women (ref), indicating that we will be able to retain this vulnerable group. Finally, because we are randomizing dyads in select geographic areas, contamination between study arms may occur, increasing chances of dilution of the treatment effect (a type ll error). As part of study Aim 1, we will assess the presence of contamination quantitatively and qualitatively and consider the need to use an alternative design such as cluster randomization for a future phase 3 trial.

In conclusion, this study will provide quantitative and qualitative evidence to determine whether a phase 3 effectiveness trial of the *Dil Mil* intervention is merited. Criteria in favor of a phase 3 trial include quantitative and qualitative data indicating that the intervention is safe and feasible; data on intermediary outcomes support the effect of the intervention on empowerment of DILs and MILs; and trends in GBV incidence and related health outcomes are in the direction that supports the effect of the intervention.
